#### Secondary Outcomes

The secondary outcomes will be the effects of the combined exercise intervention on global cognition, motor symptoms severity, and biomarker levels. These outcomes will be measured at baseline and at week 26 postintervention for both the exercise and control groups. Global cognition will be assessed using MoCA. Motor symptoms severity will be assessed using the MDS-UPDRS motor score (part III). Changes in neurotrophic (BDNF), inflammatory (CRP), and neuroendocrine (klotho and cortisol) biomarker levels will be assessed using blood, saliva, and CSF samples.

#### Exploratory Outcomes

The study will collect various other measures that may respond to exercise. This includes a cognitive battery, various measures of motor function and fitness, and participant-reported outcomes.

Cognitive battery: paper-based assessments (Trail Making Test and Alternating Verbal Fluency) and tablet-based assessments (NIH [National Institutes of Health] Toolbox) will be performed. Cognitive categorization will also be completed by the investigator to assess if the participant has normal cognition, mild cognitive impairment, or dementia.6-minute walk test: participants will be asked to walk for 6 minutes at a comfortable speed. The distance walked will be measured.Maximum volume of oxygen consumption (VO2peak): under the direction of a trained exercise physiologist, participants will walk on a treadmill beginning at 0% grade at a speed that elicits approximately 70% of their age-predicted HRmax. The incline of the treadmill will increase by 2% every 2 minutes until either the participant reaches severe fatigue that forces cessation of exercise or if any of the end points of exercise testing are met. The end points that will be used to stop the exercise test before volitional fatigue include the development of (1) chest pain or discomfort; (2) a fall of systolic blood pressure of 10 mm Hg or greater from the peak level with increasing exercise intensity; (3) excessive rise in blood pressure: diastolic blood pressure >115 mm Hg and/or systolic >220 mm Hg; (4) signs of poor perfusion: light-headedness, confusion, ataxia, pallor, cyanosis, nausea, or cold and clammy skin; (5) shortness of breath, wheezing, leg cramps, or claudication; (6) failure of HR to increase with increased exercise intensity; (7) participant requests to stop; and (8) failure of testing equipment. The VO2peak will be measured and used as an indicator of fitness level.Hand-grip and knee extensor strength testing: handgrip strength will be measured using a handheld digital dynamometer, and knee extensor strength will be measured using isokinetic dynamometry.Participant-reported outcomes of quality of life, fatigue, and mood: the Parkinson’s Disease Questionnaire-39 (PDQ-39), Parkinson’s Disease Fatigue Scale (PFS-16), Parkinson Anxiety Scale (PAS), Apathy Scale (AS), University of California, Los Angeles (UCLA) Loneliness Scale, and BDI-II will be completed. The PDQ‐39 is a self-report questionnaire of 39 items, anchored on a 5‐point Likert scale, to assess PD-specific health‐related quality of life. The PFS-16 was designed to tap a single construct encompassing the physical aspects of fatigue and their impact on the participant’s daily function. The PAS is a 12-item observer or participant-rated scale with 3 subscales for persistent anxiety, episodic anxiety, and avoidance behavior that provides a reliable measurement of the severity of anxiety symptoms in patients with PD. The AS consists of 14 items regarding different dimensions of apathetic behavior. The UCLA Loneliness Scale consists of 20 items designed to measure feelings of loneliness and social isolation. The BDI-II consists of 21 items that are designed to assess the severity of symptoms of depression.Experiences of daily living: the MDS-UPDRS Part I and II are used to evaluate various aspects of PD, including nonmotor and motor experiences of daily living and motor complications. Penn’s Parkinson’s Daily Activities Questionnaire-15 (PDAQ-15): the PDAQ-15 is an item-response theory-based questionnaire that assesses cognitive instrumental activities of daily living.Patient Global Impression of Change: this is a 7-point self-report questionnaire depicting the patient’s rating of overall improvement.Clinician’s Global Impression of Change: this is a 7-point clinician-rated measure depicting the clinician’s rating of overall improvement.

### Harms

Overall, the potential risks associated with participation in this study are of low risk. We do not anticipate any harm from this study; however, possible harms include muscle soreness or strains, falls, and pain or bruising associated with blood draws and lumbar puncture. The study investigator will be responsible for determining whether an AE is expected or unexpected. An AE will be considered unexpected if the nature, severity, or frequency of the event is not consistent with the risk information previously described for the study procedures and provided in the consent form. All harms will be documented, and any AEs occurring on site that are serious or unexpected AND definitely, probably, or possibly related to the study will be reported to the UCSF IRB within 5 working days. All AEs will be reported in the trial publication.

### Participant Timeline

The complete schedule of activities for participants is provided in Multimedia Appendix 3. This includes prescreening, screening and baseline visits, weekly phone calls, and week 26 visits. Assessments for each visit and intervention period are also noted. Additional visits will be scheduled as needed, such as if there are safety concerns with the exercise intervention.

### Sample Size

We based the sample size calculations on the secondary outcomes of efficacy. Since adherence and feasibility can only be evaluated in the exercise group and are not collected in the control group, it is not possible to calculate power comparing these outcomes between groups. The power and sample size analysis is based on the biomarker of interest, klotho, and the global cognition measure, MoCA. Based on prior studies describing changes in klotho plasma levels with exercise in healthy sedentary adults [33,34], a sample size of 14 participants per group is expected to detect an effect size of 100  pg/mL, considering a type I error of 0.05 with a statistical power of 0.85. Assuming a maximum attrition rate of 12%, we decided to recruit a total of 31 participants (16 participants in the exercise group and 15 in the control group). With respect to cognition, prior endurance exercise and resistance training studies show benefits on cognition at 6 or 12 months [17,35], but Chang et al [36] have shown that endurance exercise for 8 weeks leads to a statistically significant improvement in MoCA (1.6-point increase). Based on our sample size of 31, we will have 80% power with a 2-sided type I error of 0.05 to detect a significant improvement in MoCA.

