### Recruitment and Retention

As with many clinical trials, recruitment can be a challenge for multiple reasons. A 26-week-long intervention poses a significant burden on participants, especially as this includes assessment visits in the clinic and 2 lumbar punctures to collect CSF. However, thus far, there has been ample interest in our study through the Movement Disorders clinic at UCSF, and we foresee no issues with completing recruitment. Our attrition rate thus far has been low, with only 2 control group participants electing to withdraw from the study and not returning for the final visit. Additionally, we are alleviating participant burden to the best of our abilities by using an at-home intervention and providing all necessary equipment. Our aim is that this, combined with frequent phone check-ins and trainer-supervised sessions, will keep adherence high.

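### The 80% power for MoCA is stated on all 31 recruited, although the plan allows 12% attrition; on expected completers the same effect has about 74 to 77% power

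*Protocol article*

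**What the plan says.** All of the sizing is in the Sample Size section of the protocol article.

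- For klotho, "a sample size of 14 participants per group is expected to detect an effect size of" 100 pg/mL, with type I error 0.05 and power 0.85.
- Attrition is then added: "Assuming a maximum attrition rate of 12%, we decided to recruit a total of 31 participants", split as 16 exercise and 15 control.
- For MoCA, the section cites an earlier study with a 1.6-point increase after 8 weeks of endurance exercise. It then says: "Based on our sample size of 31, we will have 80% power with a 2-sided type I error of 0.05", the target being "to detect a significant improvement in MoCA". No SD, SD of change or correlation is given. The 1.6 points are not said to be the difference between arms on which the power rests.

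The section on participant retention and complete follow-up says that the 12% was allowed for in the sample size analysis, and that two participants had been lost with two still to be randomised. The Recruitment and Retention part of the Discussion places both losses in one arm: "only 2 control group participants electing to withdraw from the study and not returning for the final visit".

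The statistical methods plan a two-way repeated-measures ANOVA of MoCA by group, and paired t tests within each group.

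**The concern.** A power figure should refer to the number of participants expected to contribute the outcome. The klotho calculation does this: it starts from 14 evaluable per group and adds participants for attrition. The MoCA sentence, in the same paragraph, uses the total after that addition and treats it as the evaluable number. The statement that attrition was accounted for is therefore true of klotho and not of MoCA.

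MoCA is the measure for the first secondary objective, global cognition. A reader who takes the 80% at face value will credit the trial with somewhat more sensitivity on that outcome than its own attrition assumption allows. Because neither the contrast nor the SD of change is named, the reader also cannot see which effect the 80% refers to.

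**Working it through.** **Inputs.** From the Sample Size section: two-sided alpha 0.05, stated MoCA power 80%, 31 recruited as 16 and 15, attrition at most 12%. From the Recruitment and Retention section: two control losses. The SD of change in MoCA is not given.

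**Test.** With two time points, the group-by-time test in a repeated-measures ANOVA is equivalent to a two-sample t test on change. Let d be the between-group difference in change divided by the SD of change. Power comes from the noncentral t distribution with df = n1 + n2 − 2 and noncentrality d / √(1/n1 + 1/n2).

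**Step 1: the plan's own figure.** Without an SD, 80% cannot be reproduced. It can only be solved backwards. At 16/15, √(1/16 + 1/15) = 0.359, and 80% power requires d = 1.04 (1.01 by the normal approximation). If the intended difference is 1.6 points, the SD of change must be 1.6 / 1.042 = about 1.54.

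**Step 2: expected completers.** 31 × 0.88 = 27.3 in total; by arm, 16 × 0.88 = 14.1 and 15 × 0.88 = 13.2, so about 14/13. With only the two reported control losses, and if the planned split holds, 31 − 2 = 29, that is 16/13.

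**Step 3: power for the same effect (d = 1.042).**

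| Completers | Noncentrality | Power | d needed for 80% |
|---|---|---|---|
| 16/15 (all recruited) | 1.042 / 0.359 = 2.90 | 80% | 1.04 |
| 16/13 (two control losses) | 1.042 / 0.373 = 2.79 | 76.7% | 1.09 |
| 14/14 (28 complete) | 1.042 / 0.378 = 2.76 | 75.6% | 1.10 |
| 14/13 (12% attrition) | 1.042 / 0.385 = 2.71 | 73.9% | 1.12 |

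The normal approximation gives 74.4% at 14/13. If 1.6 points is detectable with 80% power at 16/15, the difference detectable with 80% power becomes about 1.67 points at 16/13 and 1.72 points at 14/13.

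**Step 4: does the answer depend on the test?** If the 80% was meant for a within-group paired t test, 1.6 points would need an SD of change of 2.13 (n = 16) or 3.08 (n = 31). Reducing n by 12% (to 14 or 27) again gives about 74%.

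**Step 5: recruited number and klotho.** 28 / 0.88 = 31.8, so 32 against 31 recruited: one participant short. For klotho, 85% at 14/14 corresponds to d = 1.18 (two-sided). For that effect, power is 83.5% at 14/13 and 85.9% at 16/13, against 85% stated.

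**The case against.** The strongest case on the other side is that the gap is small and concerns a secondary outcome in a trial that calls its efficacy part a pilot. Losses so far are 2 of 29 randomised, about 7%. Participants who stop exercising are asked to return for the week 26 assessments, so stopping exercise need not mean a missing MoCA. The full protocol, version 1.6, is not shown and may hold the SD. All of this stands, and it limits the point to a correction of wording. It does not remove the point: the article prints one power figure tied to one number of participants, and that number does not fit the attrition assumption in the same paragraph. Multiple imputation is unlikely to recover much, because clinical assessments are made only before and after the study.

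A reader might infer more than the documents support:

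- **That 31 is the wrong number, or that klotho is underpowered.** The shortfall is one participant, and klotho power stays at 84 to 86%. The 12% is an overall rate, so comparing it with losses in the control arm alone proves little. The count of 13 controls also assumes the planned split, which simple randomisation does not guarantee.
- **That MoCA power is really far lower.** For 1.6 points, power at 16/15 and then 14/13 would be 93% and 89% with an SD of change of 1.25, 82% and 76% with 1.5, 58% and 52% with 2.0, 41% and 36% with 2.5, and 30% and 27% with 3.0. These SDs are assumptions. No document supplies one, so neither end of the range can be claimed.
- **That no MoCA effect is named at all.** The 1.6 points are there. What is missing is a statement that they are the between-group difference powered for.
- **That a null MoCA result will be read as conclusive.** The article does not say so, and promises only preliminary evidence.

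**Conclusion.** The point holds for the MoCA power sentence and no further. The 80% is stated on the recruited total, while the plan itself expects to lose up to 12% and says that this was taken into account. If 80% is right at 16/15, power is about 74% at the planned maximum attrition and 77% with the two control losses reported, a fall of 3 to 6 percentage points.

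This rests on three assumptions: that the 80% is correct for 31, that the comparison is between groups on change (a paired test gives nearly the same fall), and, for the 77%, that the planned 16/15 split holds. The absolute power for 1.6 points cannot be judged without an SD of change.

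**What to change.** Restate the MoCA power on expected completers (about 27 to 29), and name the contrast, the difference and the SD of change. For example: with 27 to 29 completers, the trial has 80% power for a between-group difference of about 1.1 SD of change, or about 74 to 77% power for the difference that would have 80% power with all 31. If 1.6 points is the intended between-group difference, say so and give the SD of change used; 80% power on completers would then need an SD of about 1.4 to 1.5. If the figure was meant for a within-group test, say that instead.

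Leave the recruited number and the klotho power as they are. The cost is a revised sentence and a slightly less favourable power figure; no extra participants are needed.

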### Recruitment

Participants will be recruited primarily from the UCSF movement disorders clinic. Participants will also be recruited from local PD support groups and PD events and symposiums, community neurology clinics, and self-referral from public registries (ie, ClinicalTrials.gov).

### Assignment of Interventions

#### Sequence Generation and Randomization

The principal investigator (PI) will generate the random allocation using a simple computer-generated randomization sequence.

Participants will be randomly assigned to either the exercise intervention or control group using a simple computer-generated randomization sequence with a 1:1 allocation ratio. The waitlisted control group will be offered the chance to participate in the exercise program after completing the final study visit.

#### Allocation Concealment Mechanism

The assignment sequence is not concealed from the investigator enrolling participants, and the allocation for each new participant is known to the research team. This transparent approach, though potentially susceptible to selection bias, is necessary due to the nature of the intervention and the small size of the study team. To address this limitation, an analysis of baseline characteristics will be conducted to evaluate the similarity of the 2 groups at the start of the study.

#### Implementation

After completing all baseline assessments, participants will be contacted by the investigator to receive their group assignment. Participants allocated to the exercise intervention group will be scheduled to start training with the Neuro Exercise Specialists within 2 weeks of randomization.

#### Blinding

Due to the nature of the intervention, trial participants are not blinded to their study intervention group (exercise vs waitlist control). The investigator completing the assessments is also not blinded, as the same investigator is needed to monitor safety and adherence.

### Data Collection and Management

### Plans for Assessment and Collection of Outcomes

Before the evaluations, all study participants will sign an informed consent form. The complete schedule of assessments for screening, baseline, and week 26 visits is provided in Multimedia Appendix 3. Only participants fulfilling all the inclusion and exclusion criteria at screening will be allowed to move on to baseline. Baseline visits must occur within 8 weeks of the initial screening visit. If screening tests and procedures were completed outside of this time frame, the investigator must rescreen the participant and determine if any of the screening tests and procedures need to be repeated.

Randomization will occur after all baseline assessments are completed. During the intervention period, the study team will have weekly check-in phone calls with participants to monitor adherence, AEs, and any changes in health status. Week 26 assessments will be performed at the 26-week time point ±3 weeks.

Participants taking anti-Parkinson medications will be asked to refrain from taking any anti-Parkinson medications for 12 hours prior to any scheduled assessment visit. The MDS-UPDRS parts I-IV will be completed while the participant is off medication. As soon as these assessments have been completed, the participant will be allowed to resume their medications as normal, and the remainder of the assessments will be completed while the participant is on medication. If a participant is to begin anti-Parkinson medication after enrolling in the study, an additional visit will be scheduled to administer the MDS-UPDRS parts I-IV with Hoehn and Yahr.

Participants will be assigned a unique participant identification number when they enroll in the study to maintain participant confidentiality. Data collected will be entered into the Research Electronic Data Capture (REDCap) system, a secure and HIPAA-compliant, web-based system. Any hard copies of the data will be stored securely at UCSF.

### Plans to Promote Participant Retention and Complete Follow-Up

A maximum attrition rate of 12% was accounted for in our sample size analysis. We currently have 2 participants left to randomize and have lost 2 to follow-up. Throughout the study, we have implemented multiple strategies to increase participant retention and minimize loss to follow-up. This includes (1) planning the intervention at home with virtual supervision for exercise sessions so participants do not need to frequently travel to the clinic; (2) the study team will offer additional phone calls, supervised sessions, or in-person assistance at the research center for any participants in need of support throughout the intervention; (3) video tutorials will be provided to participants, so they feel comfortable using the equipment and completing the exercises; and (4) trainers will be available to make any exercise modifications as necessary so participants can continue to complete the intervention.

### Data Management

Data collected for this study will be carefully filed and securely stored in the research offices at UCSF. Participant-identifying information, such as contact information, will be stored separately from the analysis datasets, which will include a unique study identification number for each participant. Data will be collected on case report forms that will be securely stored in locked cabinets. Deidentified data will be entered into the REDCap system, a secure and HIPAA-compliant, web-based system.

### Statistical Methods

#### Baseline Analyses

Means, SDs, medians, ranges, frequencies, and percentages will be used to describe baseline characteristics such as age, sex, education, race and ethnicity, disease duration, levodopa equivalent dose, Hoehn and Yahr stage, MDS-UPDRS motor score (part III), and MoCA. The baseline measures will be compared between the control and exercise intervention groups.

#### Statistical Methods for Primary and Secondary Outcomes

The primary outcomes are feasibility, adherence, and safety of the combined exercise program. To assess feasibility, we will estimate the overall average %HRmax for endurance training and average repetition maximum for resistance training and their corresponding 95% CIs for the exercise group at 26 weeks. We will then compare the average to the intended target intensity (82.5% for endurance exercise and 10-RM for resistance training) using a 1-sample *t* test (*α*=.05). We will use repeated measures ANOVA of weekly %HRmax and linear mixed models to assess any trends over time from weeks 7 to 26, including a random effect for time within participant as sample size permits. To measure adherence in the exercise group, the average number of days per week exercised and the duration of time (minutes) exercised at the specified intensity will be calculated. Achievement of the adherence (hypothesized to be at least 3 d/wk) will be tested using 1-sided, 1-sample Student independent group *t* tests. To assess safety, the incidence of individual AEs (including serious AEs) and exact CIs will be calculated. We will use Fisher exact or Poisson exact tests to compare exercise and control groups for AEs that are definitely, probably, or possibly related to the exercise intervention as categorical variables.

Secondary outcomes are changes from baseline in global cognitive function, motor function, and circulating biomarkers in both the exercise and control groups. Two-way repeated-measures ANOVA will be conducted to test for differences in MoCA from baseline to week 26 by group. Within each group, paired samples Student *t* tests will be conducted to test differences in MoCA from baseline to week 26. We will also examine a difference in differences analysis within and between groups overall using ANOVA. If data permit, we will use mixed-effects linear models, with time (baseline and week 26) and group (exercise and control) as the fixed effects and participant as the random effect within each model, to determine the association between change in MoCA and each of the following covariates separately to identify important differences: age, sex, education, disease duration, disease severity (defined by Hoehn and Yahr stage, MDS-UPDRS), and use of PD medications (calculated levodopa equivalent dose). Similar analysis will be performed as above to examine differences in MDS-UPDRS motor score (part III) and circulating biomarkers (neurotrophic: BDNF; inflammatory: CRP; neuroendocrine: klotho and cortisol) from baseline to week 26.

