### Explanation for the Choice of Comparator

The exercise intervention for this study is a combined endurance and resistance exercise intervention. This intervention was chosen as it has high clinical relevance–an ideal exercise prescription for PD includes both exercises to target the cardiopulmonary and musculoskeletal systems [28]. For this combined intervention, the frequency of endurance exercise is 3 times per week, and resistance exercise is 2 times per week. The endurance exercise protocol was modeled after the Study in Parkinson’s Disease of Exercise Phase III clinical trial [30]. Endurance exercise will be performed at a high intensity with a target HR zone of 80%‐85% of maximal heart rate (HRmax). Treadmill exercise was chosen as it allows participants to follow a regular rhythmic stimulus and allows participants to keep a consistent speed and grade, which should help maintain HR in the target zone. The 80%‐85% HRmax zone is calculated using a measured HRmax from a baseline cardiopulmonary exercise test. Using a measured HRmax instead of estimating with equations is particularly important in PD, as there may be increased prevalence of autonomic dysfunction affecting HRmax in PD [31]. The resistance training protocol chosen for this study is modeled after a resistance training program in PD participants with similar disease stage and study duration as our proposed study [32].

The control group was chosen to test the hypothesis that the combined endurance and resistance exercise intervention benefits cognition and motor signs of PD more than best medical management, which usually involves prescribing anti-Parkinson medication but no exercise. Few studies have looked at a combined endurance and resistance exercise intervention in PD. This study will demonstrate how a combined intervention may benefit cognitive and motor signs of the disease and influence circulating biomarkers compared to usual care.

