#### Primary Outcomes

The primary outcomes for the study are feasibility, adherence, and safety of the combined exercise intervention. Adherence and feasibility will only be evaluated in the exercise group. Feasibility will be measured using the average percentage of HRmax for endurance exercise sessions and the average repetition maximum for resistance exercise sessions. Adherence will be measured using the average number of days exercised per week, the duration of exercise for resistance exercise, and the duration of exercise at target HR intensity for endurance exercise. Participants will keep track of exercise sessions using exercise diaries, which investigators will use to assess adherence. Data from Polar HR monitors will be used to assess feasibility. Safety will be measured by the incidence of adverse events (AEs) and serious AEs in the exercise and control groups.

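### Endurance feasibility is tested against the single value 82.5% HRmax although the prescription is an 80%-85% zone, so neither result of the test shows whether the target intensity was reached

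*Protocol article*

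**What the plan says.** Under Explanation for the Choice of Comparator, the prescription is a range: "Endurance exercise will be performed at a high intensity with a target HR zone of" 80% to 85% of measured HRmax. Intervention and Comparator repeats it and describes weekly coaching to stay within it.

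Under Primary Outcomes, "Feasibility will be measured using the average percentage of HRmax for endurance exercise sessions", in the exercise group only. Feasibility stands beside adherence and safety, with no ranking among the three. Table 1 sets the window at weeks 7-26.

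Under Statistical Methods for Primary and Secondary Outcomes, averages are estimated with "their corresponding 95% CIs for the exercise group at 26 weeks". The text goes on: "We will then compare the average to the intended target intensity". The reference values are "82.5% for endurance exercise and 10-RM for resistance training", and the method is a one-sample t test at alpha .05. No direction, margin or zone limit is attached to this test, and no result is named as showing feasibility. By contrast, achievement of the adherence target in the same paragraph "will be tested using 1-sided, 1-sample Student independent group" t tests, against a minimum of 3 days per week.

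**The concern.** The hypothesis tested is not the one prescribed. A group averaging 81% or 84% is training as instructed, yet both values belong to the alternative hypothesis. Failing to reject 82.5% in a small group is absence of evidence, and it becomes more likely as participants become more variable. If the test result is carried into the conclusion, a consistent group inside the zone can be reported as departing from target, while a scattered group below the zone can be reported as not differing from it. The Conclusions and Potential Impact section looks ahead to showing that the programme is safe and feasible, so a primary claim depends on this comparison.

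**Working it through.** **Inputs from the article.** Zone 80% to 85%; reference value 82.5%; one-sample t test, alpha .05; 16 participants in the exercise group (Sample Size).

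**Inputs assumed.** The between-participant SD of average %HRmax is not given, so a range is shown, in percentage points. The test is taken as two-sided because no direction is stated and the neighbouring adherence test is labelled one-sided. All 16 are taken as analysed; the two withdrawals reported under Recruitment and Retention were in the control group.

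**Step 1: reproduce the article's figures.** (80 + 85)/2 = 82.5, so the reference value is the midpoint of the zone. 14/(1 − 0.12) = 15.9, which rounds up to the stated 16. No power is stated for the feasibility test.

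**Step 2: observed means that are not significant.** The range is 82.5 ± t(0.975; 15 df) × SD/√16 = 82.5 ± 2.131 × SD/4.

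| SD | Half-width | Not significantly different from 82.5% |
|---|---|---|
| 2 | 1.07 | 81.43 to 83.57 |
| 3 | 1.60 | 80.90 to 84.10 |
| 5 | 2.66 | 79.84 to 85.16 |
| 8 | 4.26 | 78.24 to 86.76 |

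Only near SD 5 does this range resemble the zone, and then by coincidence. For an observed mean of 79%, the SD at which the result changes is (82.5 − 79) × 4/2.131 = 6.57. The same mean is significant below that SD and non-significant above it.

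**Step 3: probability of a significant result.** Noncentral t with 15 df and noncentrality δ = (true mean − 82.5)/(SD/4). For a mean of 81% and SD 2, δ = −1.5/0.5 = −3.0, which gives 80%. For a mean of 79% and SD 8, δ = −3.5/2 = −1.75, which gives 37% significant and 63% not.

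| SD | True mean 81% or 84% (in zone): declared different | True mean 79% (below zone): not declared different |
|---|---|---|
| 2 | 80% | <1% |
| 3 | 46% | 1% |
| 4 | 29% | 10% |
| 5 | 20% | 25% |
| 8 | 11% | 63% |

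**Step 4: does direction rescue the test?** A one-sided test for a mean below 82.5% still rejects a true mean of 81% in 89% of cases at SD 2 and 60% at SD 3, and it misses a true mean of 78% in 31% of cases at SD 8. A one-sided test for a mean above 82.5% rejects at most 5% of the time for any true mean at or below 82.5%, so it cannot credit the lower half of the zone.

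**Step 5: the interval judged against the zone.** Rule: the lower one-sided 95% limit exceeds 80%. Now δ = (true mean − 80)/(SD/4), with critical value 1.753. For a mean of 82.5% and SD 3, δ = 2.5/0.75 = 3.33, which gives 94%.

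| SD | True mean 82.5%: passes | True mean 79%: passes |
|---|---|---|
| 3 | 94% | <1% |
| 4 | 77% | <1% |
| 5 | 60% | 1% |
| 8 | 33% | 2% |

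Greater variability now makes a pass harder for a group in the zone, and a group below the zone rarely passes. The rule has a cost inside the zone as well: a true mean of 81% passes 60% of the time at SD 2 and 36% at SD 3.

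**The case against.** The best reply is that the article never says feasibility stands or falls with this p-value. It puts estimation with a 95% CI first, and it also plans weekly trends and minutes at target intensity. It states neither sidedness nor a rule that non-significance means feasible, and such a rule may stand in an analysis plan that is not shown. This is correct. A reader might infer a written two-sided pass/fail rule, but the article contains none. What remains is that the article itself fixes the test and its reference value, and Step 4 shows that the choice of direction does not repair them.

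The second reply is that the two errors need different SDs: in-zone departures are flagged mainly at SD 3 or less, and below-zone means are missed mainly at SD 6 or more. At SD 4, a true mean of 79% is flagged 90% of the time and 81% or 84% only 29%, so the test mostly separates the groups. This stands too. The test does not mislead at every SD, and the two errors are not both large at once. But its behaviour depends on an SD that nobody has stated.

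A reader might also infer that warm-up and cool-down pull the session average below target even with perfect compliance. The article does not say that those minutes enter the average. Even if they did, the shortfall would not be certain: 30 minutes at 85% and 10 at 75% give (30 × 85 + 10 × 75)/40 = 82.5%. The open question is only which minutes are averaged.

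**Conclusion.** The point holds as a mismatch between the stated test and the prescription. A comparison with 82.5% cannot by itself support or refute the claim that participants trained at the intended intensity. Under the two-sided reading with 16 participants, a mean 1.5 points from the midpoint and inside the zone is declared different 20% to 80% of the time for SD 5 down to 2. A mean one point below the zone escapes 10% to 63% of the time for SD 4 up to 8. These sizes rest on assumed SDs; the logical defect does not. The planned interval already holds most of what is needed, but the article ties the comparison to the midpoint. The point concerns the endurance half of one primary outcome. Calling it the trial's main primary outcome would go beyond the article, which does not rank the three.

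**What to change.** Before analysis begins, drop the point test against 82.5% as the basis for the feasibility conclusion. State instead that the target endurance intensity was reached if the lower one-sided 95% confidence limit of mean %HRmax over weeks 7-26 exceeds 80%. Report the planned 95% CI against both 80% and 85%. The upper comparison is needed because the lower-limit rule alone would almost always pass a group training well above the zone, for example at 88% with SD 5. The one-sided 95% limit is the lower end of a two-sided 90% interval, so name it separately from the 95% CI.

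As a clarification only, state that average %HRmax is taken over the 30-minute target segment.

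The cost is wording: the same heart-rate files are used, with no new data or participants. The price is that feasibility must be demonstrated. With 16 participants and a true mean of 82.5%, power is 94% at SD 3, 77% at SD 4, 60% at SD 5 and 33% at SD 8. With a large SD, a failure to meet the criterion should be reported as inconclusive unless the interval lies below 80%.
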